#### Randomization criteria

- Criteria set out above (age, diagnosis, consent).

- Evidence of exacerbation (Score ≥40 on the YGTSS).

- No contraindication due to the exclusion criteria.

- Patients who fulfil these criteria will be included, randomly, in one of the groups.

#### Randomization, blinding and assignment to treatment group

Randomization will be centralized and performed immediately after the inclusion of an eligible patient. The allocation envelopes will be serially numbered to ensure that allocation concealment is maintained within the pharmacy department at each hospital. A set of opaque envelopes marked with the letter A or B will be used to include patients in either the experimental or the control group. These envelopes will be kept in the pharmaceutical department responsible for dispensing the corresponding medication. Randomization to either the treatment or the placebo group will only be performed when a patient, suffering exacerbated TS, is considered eligible to receive the medication included in this study.

#### Instrumentation

The clinical data and the YGTSS score at the onset of the period of exacerbation of the clinical condition (t0) will be noted. The parents/guardians will be informed, and on receipt of their informed consent, the previously randomized medication will be provided. This medication is to be taken at the patient's home, and follow-up will be performed, at the healthcare clinic, at 15(t1), 30(t2), 60(t3) and 90(t4) days. PET will be performed at the start and end of the experimental period, for 15 patients. The psychological impact of the treatment on the families concerned will be measured using the Psychological General Well-Being Index (PGWBI) [30].

#### Evaluations

The clinical diagnosis of TS will be confirmed, and the YGTSS score ascertained, so that the patient may be included in the study and any subsequent fall in the global score recorded (at t0, t1, t2, t3 and t4). Metabolic changes in baseline and post-treatment PET will be recorded. The PGWBI will be determined at the start and end of the study period.

#### Withdrawal of individual patients

Patients may withdraw from the study at any time, for any reason and without suffering any sanction for doing so. The researcher-collaborator, after consulting with the principal investigator and the study coordinator, may also interrupt the treatment programme if the fact of continuing this treatment, in his/her opinion, would be prejudicial to the patient's welfare. If a patient withdraws or is withdrawn from the study, follow-up to day 90 should be continued whenever possible.

#### Follow-up of patients who withdraw from the study

Any patients whose treatment is withdrawn will continue to be followed up until the event in question is resolved or until, in the researcher's opinion, important changes in the patient's health state are unlikely to occur. The follow-up reports at 15, 30, 60 and 90 days will be completed for all patients who received medication (including placebo) during this study.

#### Suspension of the study

Should there occur severe adverse events related to the administration of the treatment, the study will be interrupted, and the researchers and the coordinator will decide whether to continue or not. Ultimate responsibility for this decision will rest with the coordinator. The relevant clinical research ethics committees and the healthcare authorities shall be informed of any decisions taken to interrupt, abandon or continue the study.

### Ethical criteria

#### Applicable regulations

The study will be carried out in accordance with the principles of the Helsinki Declaration, specifically the EMEA/CPMP declaration on the use of the placebo in clinical trials, with respect to the revised Helsinki Declaration, and in accordance with the guideline for Good Clinical Practice (CPMP/ICH/135/95 – 17 July 1996), as well as local regulations.

#### Recruitment

The study protocol was submitted to the Ethics Committee of the Hospital Costa del Sol (Marbella, Spain) for approval. Implementation of the study began after the Spanish national healthcare authorities formally approved it. Although patients will be informed that they are free to abandon the study at any time, we shall seek to recruit those offering the maximum probability of remaining within the study until its conclusion.

#### Informed consent for minors

After identifying candidate patients for inclusion in the clinical trial, the children will be given an oral and written explanation of the study. The parents/guardians will be provided with all available information and any complementary information they might require, and they will be given an information sheet so that their informed consent for the child to participate in the trial may be obtained. Once this has been signed, the form should be given to the researcher when the child attends the clinic for treatment of exacerbated TS (t0).

#### Liability for injury

An insurance policy for civil liability will be subscribed to cover any injuries that may arise from the performance of the study.

### Treatment details

#### Dosage and administration of medication

The medication used in the trial will be administered orally, at the patients' homes. The following medication will be provided:

Magnesium pidolate 0.5 mEq/Kg/day, divided to be taken twice daily. This should not be taken in conjunction with calcium or dairy products.

Pyroxidine alpha-aketoglutarate 2 mg/Kg/day, once daily.

#### Preparation and labelling of treatment procedures

The medication for the trials will be prepared, labelled and stored by the pharmaceutical service. The active principles of the treatment group were obtained via commercially available drugs. The placebo used was created in the hospital's pharmacy department, emulating the excipients and volume of the experimental medication. Procedures for reducing the volume of medication per pack will be implemented in accordance with ICH requirements. The study coordinator will supervise all procedures applied in this respect.

#### Other medication allowed

The patients will continue taking their usual medication to control TS symptoms or associated comorbid pathologies. Moreover, they will continue receiving any pre-existing psychological support treatment.

In addition, they will continue taking any medication prescribed prior to their entering the study, for any other concurrent illness.

### Specific methods

#### Evaluation of effectiveness

The clinical evaluation of the patients' tics will be carried out by applying the Yale Global Tic Severity Scale (YGTSS) [29]. This scale has been validated for the study of motor and phonic tics for children with TS, in comparison with other scales such as the Shapiro Tourette Syndrome Severity Scale and the Tourette Syndrome Global Scale. It was designed for studying TS and other disorders that provoke tics, and functions by evaluating the number, frequency, intensity, complexity and degree of interference of motor and phonic tics. The YGTSS is applied by means of a semi-structured interview with multiple informants (generally, the parents) who assess the child's tics over a period of at least one week. The translation into Spanish and its adaptation to local conditions were previously validated by the authors of the present paper, in a prior study [31].

#### Measurement instruments

**The Yale Global Tic Severity Scale**. The Spanish version of the YGTSS will be used. Scoring on this scale ranges from 0 to 100 points. A score of 40 or more on the YGTSS at t0 is defined as a state of exacerbation and therefore a necessary condition for the patient's inclusion in the study.

**PET **will be carried out at the beginning and end of the study in order to detect metabolic changes that may be related to the effectiveness of the treatment. Qualitative changes in the metabolism pattern within the prefrontal cortex and in the basal nuclei will be evaluated. This will be complemented with a quantitative study of the normalized rates of metabolism in such zones.

The Spanish version of the **Psychological General Well-Being Index **will be calculated for the parents, at the beginning and end of the study in order to assess the psychological repercussions of the treatment on family life [30,32]. This scale indicates the subjective feelings and psychological well-being (or otherwise) during the past week.

#### Adverse events

Any adverse event notified spontaneously by the subject, or observed by the researcher or by the research team will be recorded on the form designed for this purpose. The researcher will classify the intensity of adverse events in accordance with the following scale:

- *Mild*: some discomfort experienced but not such as to interrupt normal daily activity.

- *Moderate*: sufficient discomfort to reduce or notably affect normal daily activity.

- *Severe*: provoking incapacity to work or perform normal daily activity.

The periodicity of the event will be classified in accordance with the following scale:

- *Single occurrence*: just one event, of limited duration.

- *Intermittent*: various episodes of an event, each one of limited duration.

- *Persistent, unlimited*: an event that has persisted over time, and is of indefinite duration.

For each adverse event, its relation with the medication taken (definitive, probable, possible, improbable, none), in the researcher's opinion, as well as any action taken as a result, will be recorded on the data collection form. The occurrence of an adverse event that is fatal, potentially fatal or incapacitating, or that requires or prolongs hospitalization, or that provokes severe congenital anomalies will be recorded as a "severe" adverse event (SAE).

All SAEs and unexpected adverse pharmacological reactions (UAPR), defined as adverse events whose nature or intensity is not in accordance with any adverse event expected, will be notified by the researcher to the study coordinator by phone, mail or fax as soon as is reasonably possible, but in any case within 24 hours of their occurrence.

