We have designed a clinical trials to evaluate the effects of magnesium and vitamin B_6 _supplements on the clinical condition of children with TS. This supplementation is authorized for children and already commercially available; therefore, our aim in the present study is to confirm a possible new indication. The study should include children up to the age of 14 years, diagnosed with TS; this age limit was chosen as it is then when a standstill or remission of the symptoms may occur. The minimum duration of treatment and follow-up for these children should be three months, in view of the natural evolution of the illness, with spontaneous remissions and exacerbations. The symptoms most easily measured are the presence and severity of tics.

We present a new therapeutic approach to TS, based on the hypothesis that a deficit of vitamins or oligoelements, or a reduction of their activity, aggravates this pathology and often provokes severe comorbidity. Moreover, we take into account that current treatment protocols are frequently ineffective among many children and present important potential side effects.

Thus, we propose the following:

Main goal – to show that, with respect to placebo treatment, the combination of 0.5 mEq/Kg magnesium and 2 mg/Kg vitamin B_6 _reduces motor and phonic tics and incapacity in cases of exacerbated TS among children aged 7–14 years.

Secondary goals – to assess the safety of the treatment, in terms of adverse events; to describe metabolic changes resulting from the treatment, as revealed by PET; and to measure the impact of this treatment on the quality of family life.

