#### Study periods

t0 Entry into the study

   When the child's parents/guardians consider a period of exacerbation is beginning, they enter the active phase of the study. The YGTSS score is assessed, taking into account that a score of at least 40 is a prerequisite for entry into the study.

   The baseline PET is carried out for patients included in the study.

   The PGWBI for the parents/guardians is calculated.

**t1 At 15 days**.

   The YGTSS is calculated.

t2 At 30 days

   The YGTSS is calculated.

t3 At 60 days

   The YGTSS is calculated.

**t4 At 90 days. End of study period**.

   The YGTSS is calculated.

   PET control.

   PGWBI for parents/guardians.

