#### General considerations

A descriptive statistical analysis will be performed, using statistics of central trend and dispersion for the quantitative variables, and frequency distributions for the categorical ones, carried out separately for the experimental and control groups. The baseline variables will be compared using these techniques. A flow diagram will be drawn to show the sequence from the initially eligible population to the one finally included in the study (refusals, dropouts, lost to follow-up, etc.), in accordance with the criteria of the CONSORT guidelines.

A comparison will be made of between-group differences between the initial and final measurements for the diverse elements of the Yale Scale, using unpaired nonparametric tests. For the final within-group comparison, paired nonparametric tests will be used non-parametric Repeat measures with adjustments for baseline imbalances and scores. The same analysis will be performed for the index of psychological well-being, measuring the repercussions of the treatment on family life.

The principal outcome variable (POV) will be taken as the change in the global score on the Yale Scale, adjusted for the baseline values. A simple linear regression model will be made for this POV, and the level of significance set at p < 0.05. Subsequently, a multiple linear regression model will be created, including the variable "Experimental/Control Group", and adjusting for any baseline variables that might be unbalanced. Statistical adjustment was performed by means of a multivariate model including the variable group (experimental and control) and concomitant treatment (Yes/No).

The safety of the treatment will be described in terms of the percentage of adverse events, and according to levels of assignation of responsibility.

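### Adverse events are captured by spontaneous report or staff observation, with no enquiry at visits described, so mild and intermittent events are likely to be under-recorded in both arms

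*Protocol article*

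**What the plan says.** Safety is a secondary goal of the trial, worded in the Background to the study as "to assess the safety of the treatment, in terms of adverse events" and repeated in the Abstract. The Adverse events section states how events reach the record: "Any adverse event notified spontaneously by the subject, or observed by the researcher or by the research team will be recorded". The same section then gives scales for intensity, periodicity and causal relation, including a category for intermittent events. Under General considerations the planned summary is descriptive: "The safety of the treatment will be described in terms of the percentage of adverse events", with a breakdown by attributed responsibility.

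On the setting, Instrumentation says "This medication is to be taken at the patient's home" and places follow-up "at the healthcare clinic, at 15(t1), 30(t2), 60(t3) and 90(t4) days". Study periods lists what is done at each visit. For t1, t2 and t3 the one entry is "The YGTSS is calculated"; t4 adds a control PET and "PGWBI for parents/guardians". The section on follow-up of patients who withdraw adds a relevant requirement: "The follow-up reports at 15, 30, 60 and 90 days will be completed for all patients who received medication", placebo included. It does not describe the content of those reports.

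**The concern.** The capture method is stated, and it is passive: someone has to volunteer the event or a member of the team has to notice it. The children are aged 7 to 14, take the study medication at home and are seen four times in 90 days. A short-lived or mild event between visits leaves little for the team to observe, and nothing described prompts anyone to mention it. Such events belong to the mild and intermittent categories that the form is meant to classify.

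What is at stake is the secondary safety aim. Its planned summary is a percentage of adverse events, and that percentage can be no better than the capture behind it. Good tolerability is also part of the case made for the treatment in the Discussion, so a low recorded percentage would carry weight with readers. The primary outcome, the change in YGTSS score, is not touched.

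**Working it through.** **Step 1: set the sections side by side.**

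| Section | What it settles about capture |
|---|---|
| Adverse events | Spontaneous notification, or observation by the researcher or team |
| Instrumentation; Evaluations | YGTSS, PET and PGWBI; no adverse-event enquiry |
| Study periods | YGTSS at every visit; PET and PGWBI at t0 and t4; no adverse-event enquiry |
| Follow-up of patients who withdraw | Reports on days 15, 30, 60 and 90 for all treated patients; content not stated |
| Follow-up after occurrence of an adverse event | What happens once an event is known; not how it is found |

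The first row carries the point, because it states a method. The others do not contradict it and do not add an enquiry. The gaps between visits are 15, 15, 30 and 30 days.

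**Step 2: reproduce the plan's sample size, since the illustration uses it.** The plan assumes means of 13 and 23, SD 10, a significance level of 0.05 and power 0.8. The standardised difference is (23 − 13)/10 = 1. The two-sided t-test calculation gives 16.7, so 17 per group; the normal approximation gives 16. Allowing for 10% dropout, 17/0.9 = 18.9, so 19 per group, and 34/0.9 = 37.8, so 38 in total. The stated figures are right.

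**Step 3: illustrate the effect of incomplete capture.** The documents give neither an adverse-event incidence nor a capture share, so both are assumed here. Let p be the true proportion of treated children with an event and c the proportion of those who are recorded. With 19 treated children, acting independently,

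P(at least one recorded) = 1 − (1 − p·c)^19.

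- p = 0.10, c = 1: 1 − 0.90^19 = 1 − 0.135 = 86%
- p = 0.10, c = 0.5: 1 − 0.95^19 = 1 − 0.377 = 62%
- p = 0.10, c = 0.3: 1 − 0.97^19 = 1 − 0.561 = 44%
- p = 0.20, c = 1: 1 − 0.80^19 = 1 − 0.014 = 99%
- p = 0.20, c = 0.5: 1 − 0.90^19 = 86%
- p = 0.20, c = 0.3: 1 − 0.94^19 = 1 − 0.309 = 69%

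The expected number of children recorded is 19·p·c. At p = 0.10 this is 1.9, 0.95 and 0.57 for the three capture shares.

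**Step 4: separate capture from small numbers.** Even with full capture, no events among 19 children would leave a one-sided 95% upper limit of 1 − 0.05^(1/19) = 14.6%. Better capture does not cure the small sample; it stops a second loss being added to it.

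**Step 5: direction of the effect on the comparison.** If capture is the same in both arms, the difference in recorded proportions is c·(p1 − p2). With assumed true proportions of 30% and 10%, the difference of 20 points becomes 15% against 5%, or 10 points, at half capture. It shrinks but keeps its sign.

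**The case against.** The best defence is that the text does not say nobody asks. It says that any event notified or observed goes on a dedicated form, which is not shown, and follow-up reports are completed for every treated child at each visit. The list in Study periods is short and not exhaustive: it omits dispensing and the clinical data noted at t0. A journal article may leave an enquiry to the full protocol or the case report form. This stands in part. The visit list alone proves little, and it would go too far to say that events can enter the record only if volunteered or noticed by chance. But the Adverse events section is detailed and describes patient notification as spontaneous. That is a positive statement of method, and the follow-up reports are not said to change it.

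Three stronger readings should be resisted.

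- A reader might infer that parents are excluded as reporters because the section names the subject. The drafting is too loose for that: Selection of subjects slides from patients to parents in the same paragraph, and parents are generally the informants for the YGTSS.
- A reader might infer that the pilot's finding of no side effects came from the same passive method, and that this trial would merely repeat it. The article does not say how the pilot collected events.
- A reader might infer a bias in favour of the experimental arm. The trial is blinded and the placebo imitates the excipients and volume of the active medication, so under-recording would be expected in both arms alike.

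The illustration has limits too. It gives each affected child one chance of being recorded, whereas a persistent event could surface at any of four visits. At least one case recorded is also not a planned outcome.

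**Conclusion.** The point holds as a weakness in a stated method, and it should be corrected. Capture by spontaneous report and observation, under home treatment with visits up to 30 days apart, is likely to under-record mild and intermittent events. Likely is as far as the documents go: they do not show that events will be missed, or how many. If blinding holds, the consequence is lower absolute percentages in both arms and a difference that is harder to see, not a reversed comparison.

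On assumed values, halving capture at 10% incidence lowers the chance of recording any affected child among 19 from 86% to 62%; at 20% incidence, from 99% to 86%. These figures rest on the assumed incidence and capture share and on independence between children. The primary analysis and the sample size of 38 are unaffected.

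**What to change.** At t1, t2, t3 and t4, before the YGTSS interview, ask parent and child one standard non-leading question: whether anything has been different about the child's health since the last visit. Use the same words in both arms and record the answer on the existing adverse-event form. Add a field marking each event as solicited or spontaneous, and report the two separately. The trial began in October 2007 and is in progress, so this flag also keeps data collected before and after the change distinguishable.

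If the follow-up reports already contain such a question, it is enough to say so in the Adverse events section, with its wording and to whom it is put.

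The cost is about a minute at visits that already take place, additional minor events to record and classify, and a protocol amendment. No extra visits are needed and the sample size does not change.

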#### Follow-up after occurrence of an adverse event

All adverse events will be observed until their remission or stabilization. Depending on the circumstances, this observation might necessitate evaluation by and/or referral to the patient's GP or to a specialist.

### Procedures and control

#### Selection of subjects

Patients diagnosed with TS will be included in a preliminary "potential subjects" group. Before undertaking any selection activity, written informed consent, signed and dated, must be obtained from the parents or guardians. The patients will be informed, before any action is taken, of the purposes and structuring of the study, and any doubts that might be expressed will be answered. It will be stressed that they have the unconditional right to withdraw from the study at any time. They will be asked to return to the healthcare clinic to begin the study procedure when they believe the child is entering a period of exacerbation of TS.

#### Study periods

t0 Entry into the study

   When the child's parents/guardians consider a period of exacerbation is beginning, they enter the active phase of the study. The YGTSS score is assessed, taking into account that a score of at least 40 is a prerequisite for entry into the study.

   The baseline PET is carried out for patients included in the study.

   The PGWBI for the parents/guardians is calculated.

**t1 At 15 days**.

   The YGTSS is calculated.

t2 At 30 days

   The YGTSS is calculated.

t3 At 60 days

   The YGTSS is calculated.

**t4 At 90 days. End of study period**.

   The YGTSS is calculated.

   PET control.

   PGWBI for parents/guardians.

